### Aim of the study

The aim of the METRO (Mesoglycan for secondary prevention of superficial vein thrombosis), a randomized controlled and double-blind study, is to evaluate the usefulness of mesoglycan for the secondary prevention of VTE, after the initial 45-day course of subcutaneous fondaparinux (2.5 mg OD), in patients with SVT of the lower limbs.

## Materials and methods

### Design of the study

The METRO study is a multicenter, phase 2, randomized, double-blind, superiority trial that compares mesoglycan 50 mg BID with a matching placebo. Using a placebo as a comparator is justified by the absence of scientific evidence on the efficacy and safety of any treatment in this setting. The METRO study is conducted in 19 Italian Units of Vascular Medicine, all with significant experience in the management of VTE. The Coordinating Centre will be the General Medicine Unit and the Thrombotic and Haemorrhagic Disorders Unit at the Department of Medicine—Padua University Hospital, Italy. The study protocol has been reviewed and approved by the Ethics Committee of the Padua University Hospital, Italy, and by those of each participating center.

Before inclusion, patients/participants are requested to sign a written informed consent form.

An independent data safety monitoring board (DSMB), blinded to the patient's treatment allocation, formed by three highly qualified clinicians in the field of VTE, will adjudicate all efficacy events, monitor patients' safety, and vouch for the data quality.

### Study population and randomization

Subjects of both sexes, > 18 years of age, with objectively documented SVT of the lower limbs, initially extended for at least 5 cm, who had completed the standard 45-day course with fondaparinux 2.5 mg OD, were asked to participate in the study. Patients could only be included if they consented to participate within two weeks from treatment withdrawal. The complete list of inclusion and exclusion criteria is reported in Table 1.

**Table 1 Tab1:** Inclusion and exclusion criteria for METRO study

Inclusion criteria	Exclusion criteria
Age ≥ 18 years Objective diagnosis of SVT of the lower limbs documented with Color Coded Doppler Ultrasound of at least 5 cm extension, not involving the last 3 cm of the great saphenous vein and of the small saphenous vein, close to the respective sapheno-femoral and sapheno-popliteal junction Completion of the initial treatment of the acute phase with fondaparinux 2.5 mg once daily for 45 days With a negative ultrasound scan for SVT recurrence/extension and/or DVT at the end of the acute phase treatment. treatment	Little adherence to the treatment of the acute phase with Fondaparinux or its premature withdrawal before the deadline of 45 days Interval between the end of fondaparinux treatment and recruitment > 15 days Mandatory anticoagulation for other clinical diseases than SVT Life expectancy < 24 months Scarce compliance or impossibility of filling or answering the questionnaires Pregnancy or breastfeeding Severe muscoloskeletal disability or prolonged immobilization Concomitant participation in another clinical trial or previous participation in the last 3 months Overt post-thrombotic syndrome with a Villalta Score > 4 Chronic lymphedema of the lower limbs Recent (< 3 months) or planned surgery for varicose veins or PTA angioplasty Dyalisis Malabsorption or malnutrition Chronic use of high doses of phlebotonics, steroids, or nonsteroidal anti-inflammatory drugs, mandatory dual antiplatelet therapy or aspirin > 160 mg once daily, central painkillers Known hypersensitivity to mesoglycan or heparin or heparinoids Intolerance to galactose or lactase enzyme deficiency Bleeding tendency

After signing the informed consent, eligible subjects will complete the screening visit. Only patients who meet the inclusion and exclusion criteria will be included.

The included patient will first undergo bilateral color-coded Doppler ultrasound (CCDU) of the lower limbs to exclude concomitant involvement of the deep venous system or an extension of the index SVT. Furthermore, blood sampling for alanine-aminotransferase, aspartate-aminotransferase, creatinine, complete blood count, prothrombin time, activated partial thromboplastin time, and C-reactive protein will be performed.

A computer-based centralized randomization, with 1:1 allocation between mesoglycan and placebo, and random variable size blocks (4 to 6 units), stratified for age (< 60 y, >  = 60 y), and gender (F/M), will be run through a dedicated application (REDCAp). Patient recruitment is expected to be completed in 24 months.

### Treatment

Patients will receive a hard capsule of 50 mg mesoglycan or a matching placebo twice daily for 12 months. Treatment packages will be labeled with a bare numerical code without reference to the content. The match between the numerical code and the package content will only be known to the packaging manager. Patients, investigators, the steering committee, and DMSC will be blinded to treatment group allocation. The blinding seal will only be opened after the database lock to allow the analysis of the study results, except for in the case of a medical emergency, for which it is considered essential to know the type of treatment.

Each participating center will keep a printed drug accountability form for each patient included in the study (drug amount delivered, consumed or returned).

### Patient flow

Medical control visits will be scheduled 3, 6, 9, and 12 months after randomization for every included patient, during which a complete evaluation of their clinical status, compliance with treatment, concomitant treatments and adverse events will be performed. At each visit, patients will also receive the revised Venous Clinical Severity Score (rVCSS), which accounts for changes in disease severity over time and in response to treatment, and the VEINES/Sym-QoL questionnaire, a disease-specific quality of life instrument for chronic venous disorders of the leg [34–39]. A CCDU examination and a blood sample will also be scheduled for the 12 month visit.

At the end of the 12-month treatment cycle, patients will enter another 12-month clinical follow-up period, during which they should not receive any experimental treatment; for a total study time of 24 months. A final visit will be scheduled 24 months after randomization in patients who complete the study course.

Patients who meet exclusion criteria at any time during the study, become pregnant, do not comply with study purposes or withdraw their consent will be censored. Patients who withdraw experimental treatment will continue to observe according to the study protocol until the end of the study. The planned flow of the patient is shown in Fig. 1.

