### Final analysis of secondary endpoints

For the analysis of the secondary efficacy endpoints, the following will be used:the Kaplan–Meier plot of the cumulative occurrence over time and the log-rank test to compare the two treatment arms,for the rVCSS scores, analysis of variance for repeated measures will be used (all available assessments for within-subject effects and the 2 treatment groups as between-subjects effect).in the case of the VEINES/Sym-Qol scores, the analysis of variance for repeated measures will be used (all evaluations available for the within-subject effect and the 2 treatment groups as the between-subjects effect).The impact of elastic compression therapy in the various endpoints will be analyzed by inserting it as a stratification factor in the related analyzes.The predictive contribution of CRP levels (subdivided by tertiles) to the primary efficacy endpoint will be analyzed by insertion as a stratification factor in relative analyzes.

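### The planned analysis of rVCSS and VEINES/Sym-QoL adjusts for neither starting severity nor the age and sex strata, and the article names no score before month 3

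*Protocol article*

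**What the plan says.** The timing of the two scores is set in *Patient flow*. The visits come first: "Medical control visits will be scheduled 3, 6, 9, and 12 months after randomization for every included patient". The scores follow: "At each visit, patients will also receive the revised Venous Clinical Severity Score (rVCSS), which accounts for changes in disease severity over time". The same sentence adds response to treatment as a reason for choosing rVCSS, and gives VEINES/Sym-QoL on the same schedule. *Study outcomes* makes both scores secondary efficacy outcomes.

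For the period before treatment, *Study population and randomization* refers to a screening visit without listing its content: "After signing the informed consent, eligible subjects will complete the screening visit". It then itemises imaging ("The included patient will first undergo bilateral color-coded Doppler ultrasound (CCDU) of the lower limbs") and laboratory work ("blood sampling for alanine-aminotransferase, aspartate-aminotransferase, creatinine, complete blood count, prothrombin time, activated partial thromboplastin time, and C-reactive protein will be performed"). Neither score appears there. Randomisation is stratified by age (below 60, or 60 and over) and by sex.

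*Final analysis of secondary endpoints* prescribes repeated-measures analysis of variance for rVCSS, using "all available assessments for within-subject effects and the 2 treatment groups as between-subjects effect". VEINES/Sym-QoL is to be analysed in the same way. No change variable and no covariate is mentioned for either score.

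**The concern.** Scores of this kind usually carry persistent differences between patients. A pre-treatment value used as a covariate removes much of that variation from the error term. The stated model does not do this, and it leaves out the two factors that were stratified at randomisation. By contrast, the Cox model for the primary endpoint does list age and sex as covariates.

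The plan is weak whichever way the open question about baseline is answered:

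- **No pre-treatment score exists.** The series begins after three months on study drug. The within-subject term then describes only month 3 to month 12 and cannot show response from the pre-treatment state, which is part of the reason given for choosing rVCSS.
- **A pre-treatment score exists.** Read literally, the analysis makes it one more repeated outcome. It cannot carry a treatment effect, so it pulls the average difference between arms towards zero.

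At stake is the chance of detecting an effect on two secondary outcomes, and what may be claimed from them. The primary endpoint is not affected.

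**Working it through.** The article gives no standard deviation, target difference or power for either score, so there is no stated figure to reproduce.

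**Step 1. Schedule against analysis.** Named time points for the scores: months 3, 6, 9 and 12 (*Patient flow*). Itemised pre-treatment procedures: ultrasound and a blood panel (*Study population and randomization*). Planned model: time within subjects and treatment between subjects (*Final analysis of secondary endpoints*). No section names a baseline score, a baseline covariate, or age and sex as terms in this model.

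**Step 2. Dilution if a baseline is one of the repeated outcomes.** Let the treatment effect be 0 before treatment and a constant d at the four later visits. The time-averaged group effect is (0 + d + d + d + d)/5 = 4d/5. The fifth measurement buys little precision in return. With unit variance and equal correlation rho between assessments, the variance of a mean of k scores is (1 + (k − 1)rho)/k. At rho = 0.5 this is 0.625 for four scores and 0.600 for five. The standard error falls by a factor of √(0.600/0.625) = 0.98, while the effect falls by a factor of 0.80. This applies to the between-group main effect and counts only months 3 to 12 after baseline.

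**Step 3. Precision gained from a baseline covariate.** Under the same assumptions, the variance for the four-visit mean is (1 + 3rho)/4 unadjusted and (1 + 3rho)/4 − rho² after adjustment. For a single visit, the ratio of adjusted to unadjusted variance is 1 − rho². The documents give no value of rho, so a range is shown.

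| rho (assumed) | Four-visit mean, unadjusted | Adjusted | Reduction | Single-visit reduction |
|---|---|---|---|---|
| 0.3 | 0.475 | 0.385 | 19% | 9% |
| 0.5 | 0.625 | 0.375 | 40% | 25% |
| 0.7 | 0.775 | 0.285 | 63% | 49% |

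**Step 4. The same in detectable differences.** Take the planned 325 per arm less the planned 10% loss, that is 292 per arm, with two-sided 5% significance and 90% power. The smallest detectable single-visit difference is (1.960 + 1.282) × √(2/292) = 0.27 SD unadjusted. Multiplying by √(1 − rho²) gives 0.26, 0.23 and 0.19 SD for rho of 0.3, 0.5 and 0.7.

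**Step 5. Strata.** If age and sex predict the scores, leaving them out after stratified randomisation makes the standard error too wide. The documents give nothing from which to size this.

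**The case against.** The strongest objection is that the absence of a baseline score is inferred from silence. A reader might conclude that none was taken, but the documents do not support that. The content of the screening visit is not listed. The article refers the reader elsewhere for the schedule ("The planned flow of the patient is shown in Fig. 1"), and that figure is not available here. A journal article may also leave the full assessment schedule to the protocol. The itemised entry procedures are visibly incomplete: the Villalta score is an exclusion criterion in Table 1, and the abstract reports the site of the index thrombosis, yet neither is on that list. Inability to complete questionnaires is an exclusion ("Scarce compliance or impossibility of filling or answering the questionnaires"), which shows that they were considered at entry, though not that they were completed then. This objection stands, and the point is limited accordingly.

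A reader might also infer that without a baseline a chance imbalance cannot be told from a drug effect, so that the comparison is invalid. That is not right either. Randomisation makes the comparison of on-treatment scores unbiased in expectation, and the type I error of the test already allows for chance imbalance. Nor does the 38.3% of patients entering with a recurrent thrombosis measure how widely these scores vary.

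The dilution argument is conditional. It needs a constant effect and inference on the group main effect. A group-by-time test is not diluted in this way, and the article does not say which term decides. A constrained longitudinal model may validly treat baseline as an outcome. These limits stand, but the article states neither alternative, and the model it does state has no covariates.

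Finally, an analysis plan that is not shown may refine the model. That does not change what the article itself fixes.

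**Conclusion.** The point holds as a weakness in the stated analysis of two secondary outcomes. The article names both scores only at months 3, 6, 9 and 12. Its model has treatment as the only between-subjects effect and uses neither a starting score nor the randomisation strata. It does not establish that no pre-treatment score was recorded.

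The cost is precision, not bias. For the four-visit mean, a baseline covariate would remove about 19% to 63% of the variance for rho of 0.3 to 0.7. For a single visit it would remove 9% to 49%. These figures assume equal correlation between assessments and a range of rho that the documents do not supply. If a baseline is used as a repeated outcome, the group main effect falls to 4/5, assuming a constant effect at months 3 to 12. If no baseline exists, no claim of change from the pre-treatment state can be made.

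**What to change.** Before the treatment codes are opened, state whether rVCSS and VEINES/Sym-QoL were recorded before the first dose, and amend the analysis text to match.

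- **If they were recorded:** analyse months 3 to 12 as the outcome, with the baseline score, age stratum and sex as covariates, or use an equivalent constrained longitudinal model. Name the term that decides the comparison.
- **If they were not:** adjust for age stratum and sex, present the result as a between-arm comparison of on-treatment levels, and make no claim of change from baseline.

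New baseline scores cannot be collected, because recruitment closed on December 31, 2022 with 570 patients randomised. The Villalta score is a weak substitute: overt post-thrombotic syndrome with a score above 4 was excluded, which narrows its range, and the article does not say that it was recorded for everyone.

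The cost is a few lines of analysis text and slightly more analysis work. Without a baseline, it also means a weaker claim.

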### Statistical considerations

All variables will be descriptively analyzed with the appropriate statistical methods: for categorical variables using frequency tables and for continuous variables with sample statistics (e.g., mean, median, standard deviation, minimum and maximum value, 25° and 75° quartile).

Unless otherwise specified, all statistical tests will be 2-tailed and at a 5% significance level.

All the primary and secondary efficacy and safety analyses will be performed in the modified intention-to-treat (ITT) population, including all randomized subjects who received at least one dose of the study drug.

Further supporting analysis will be performed in the per-protocol population, which will include all randomized subjects who were complying with treatment, that is, taking at least 65% of the intended dose units of the study drug.

Subjects who are randomized and who have taken any amount of study drug will not be replaced for any reason. Subjects who will be randomized but withdraw their consent before taking the study drug may be replaced, although they will not lose their unique identifier.

Subjects who leave the observation without manifesting the endpoint will be considered censored, participating in the risk during the observation period. For subjects who do not appear for clinical evaluations at 12 and 24 months of observation, every effort will be made to know a possible outcome of interest for the study, making them evaluable for endpoints.

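### Censoring randomised patients at a later exclusion criterion, pregnancy or non-compliance is potentially informative and conflicts with the declared modified ITT analysis

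*Protocol article*

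**What the plan says.** Four statements in the protocol article bear on who is followed and counted.

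- **Patient flow, censoring.** The rule for randomised patients is: "meet exclusion criteria at any time during the study, become pregnant, do not comply with study purposes or withdraw their consent will be censored".
- **Patient flow, next sentence.** "Patients who withdraw experimental treatment will continue to observe according to the study protocol until the end of the study".
- **Statistical considerations, population.** All primary and secondary efficacy and safety analyses are to be "performed in the modified intention-to-treat (ITT) population, including all randomized subjects who received at least one dose of the study drug". A supporting per-protocol set is restricted to those "taking at least 65% of the intended dose units of the study drug".
- **Statistical considerations, censoring.** "Subjects who leave the observation without manifesting the endpoint will be considered censored".

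The exclusion criteria that can act as triggers are in Table 1. They include "Life expectancy < 24 months", "Severe muscoloskeletal disability or prolonged immobilization", recent or planned varicose-vein surgery, mandatory anticoagulation for another disease, bleeding tendency and poor compliance. Under Study outcomes, the primary endpoint is the first of several thrombotic events or death during the treatment period. Under Final analysis of the primary endpoints, prolonged immobilisation and recent surgery are among the candidate risk factors for DVT and PE.

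**The concern.** Log-rank, Kaplan–Meier and Cox analyses treat a censored patient as having the same future risk as those still under observation. Here some censoring is triggered by a change in that risk. Read literally, a patient who becomes immobilised is censored and a later DVT is not counted. A patient found to have a life-limiting illness is censored and the death is not counted, although death is a primary component.

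The rule also changes the question answered. Modified ITT with follow-up to month 12 estimates the effect of assignment in everyone who started treatment. Censoring at these states estimates the effect only while patients remain free of them. The two can differ even when the states are equally common in both arms. If they are more common in one arm, through bleeding tendency or anticoagulation for instance, the comparison may be distorted further, in a direction that cannot be known beforehand.

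Finally, two statisticians could build different primary datasets from this text.

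**Working it through.** **The passages side by side**

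| Patient after randomisation | Patient flow, censoring sentence | Other text |
|---|---|---|
| Becomes immobilised, has vein surgery, or has life expectancy under 24 months | Censored | Stays in modified ITT |
| Stops study drug | Not named | Observed to end of study |
| Stops study drug because of pregnancy or a new exclusion criterion | Censored | Observed to end of study |
| Takes less than 65% of doses | Unclear: study purposes is undefined, but poor compliance is in Table 1 | Stays in modified ITT, leaves the per-protocol set |

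The third row is a direct contradiction. The first conflicts with the analysis set.

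**Inputs from the protocol:** 325 patients per arm, 12-month risks of 15.0% and 7.8%, HR 0.50, two-sided alpha 0.025. The risks and HR agree: ln(0.922)/ln(0.85) = 0.500. Without dropout, expected events are 325 × (0.150 + 0.078) = 74.

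**Assumptions, not in the protocol:** a fraction f = 10% in each arm reaches a trigger at a uniformly distributed time within 12 months, and the hazard is then multiplied by k = 3 or 5. There is no dropout.

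**Formulas.** Let a and b be an arm's 12-month hazards before and after the trigger. Survival to month 12 of a triggered patient, averaged over trigger time, is S(a,b) = (e^−a − e^−b)/(b − a).

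- Risk with full follow-up: (1 − f)(1 − e^−a) + f[1 − S(a,b)]
- Proportion with a counted event if censored at the trigger: (1 − f)(1 − e^−a) + f[1 − (1 − e^−a)/a]
- Kaplan–Meier risk if censored at the trigger: 1 − e^−a

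**Step 1, placebo.** With a = h and b = kh, setting the full-follow-up risk to 15% gives h = 0.1489 (k = 3) or 0.1390 (k = 5). Check for k = 3: S = (0.8617 − 0.6397)/0.2978 = 0.745, and 0.9 × 0.1384 + 0.1 × 0.2548 = 0.150. The censored Kaplan–Meier risk is 1 − e^−0.1489 = 13.8%, or 1 − e^−0.1390 = 13.0%. The crude proportions with a counted event, 13.2% and 12.3%, are lower, but the protocol plans Kaplan–Meier.

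**Step 2, drug effect unchanged after the trigger** (mesoglycan a = h/2, b = kh/2).

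| | k = 3 | k = 5 |
|---|---|---|
| Events, full follow-up | 325 × (0.150 + 0.0783) = 74.2 | 325 × (0.150 + 0.0790) = 74.4 |
| Events counted | 325 × (0.1316 + 0.0682) = 64.9 | 325 × (0.1234 + 0.0638) = 60.8 |
| Events not counted | 9.3 | 13.6 |

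With f from 5% to 15%, the loss runs from 5 to 19 events. The HR stays about 0.50.

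**Step 3, no drug effect after the trigger** (mesoglycan a = h/2, b = kh). Counted events are as in step 2 and the censored HR is (h/2)/h = 0.50. With full follow-up the mesoglycan risk is 8.71% or 9.11%:

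- k = 3: HR ≈ ln(0.9129)/ln(0.85) = 0.56
- k = 5: HR ≈ ln(0.9089)/ln(0.85) = 0.59

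**Step 4, power** = Φ(√D × |ln HR|/2 − 2.241), where D is the number of events.

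| | Full follow-up, k = 3 / 5 | Censored, k = 3 / 5 |
|---|---|---|
| Effect unchanged | 77% / 77% | 71% / 68% |
| No effect after trigger | 62% / 55% (77.0 and 78.3 events) | 71% / 68% |

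The ordering reverses between the rows. Power is therefore not a robust argument for or against the rule. That 74 events give 77% power and not the planned 90% is a separate sample-size matter.

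**The case against.** The best defence is that the protocol does not run an on-treatment analysis. Patients who stop study drug remain under observation, and low intake is handled elsewhere: by the 65% per-protocol set, by a stratification variable under Treatment compliance, and by a Cox covariate. Those provisions presuppose that poorly compliant patients remain in the main analysis. This stands. A reader might infer that the rule turns modified ITT into an on-treatment analysis, or that every non-adherent patient is censored. The text supports neither. Non-compliance with study purposes is not defined as low drug intake, and the result is a hybrid. Poor compliance is also an exclusion criterion, however, so the overlap is real and needs resolving.

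A reader might also infer that patients are always censored just as their risk rises. That fits immobilisation, surgery and short life expectancy. Mandatory anticoagulation may lower risk, and other criteria, such as lactase deficiency, have no evident direction.

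It can fairly be added that the trigger frequency and hazard multipliers are assumptions, that some of these patients may already lie within the planned 10% loss per arm, and that the protocol promises every effort to learn outcomes for patients who miss the 12- and 24-month visits. These points limit what can be said about size. They do not remove the conflict: the retrieval sentence concerns missed visits, and it does not say that an event found after a censoring trigger would count. Censoring at withdrawal of consent to follow-up is unavoidable and is no fault.

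**Conclusion.** The point holds as a stated rule that conflicts with the declared population and with the sentence that follows it. It is not a detail left to an unseen analysis plan. The censoring is potentially informative because some triggers are prognostic by the protocol's own lists.

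The main harm is to the estimand. If the drug has no effect after the trigger, the censored analysis shows HR 0.50 where full modified ITT follow-up would show 0.56 to 0.59, even with equal trigger rates by arm. If the effect persists, the HR barely moves, and the cost is 9 to 14 uncounted events and a placebo risk read 1.2 to 2.0 percentage points too low. Both results assume 10% triggered, a 3- to 5-fold hazard afterwards and no dropout. Triggers that lower risk would shift the placebo risk the other way. The documents do not establish the actual size or direction, nor that the rule necessarily costs power.

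**What to change.** For the primary analysis, keep every modified ITT patient in the assigned arm until first event or month 12. Censor only at withdrawal of consent to follow-up, loss to follow-up, or the end of the 12-month period. State that a post-randomisation exclusion criterion, pregnancy or non-compliance does not end outcome follow-up; this concerns outcome ascertainment only and leaves treatment decisions untouched. Report censoring at those states as a sensitivity analysis. Reconcile Patient flow with Statistical considerations, including what non-compliance with study purposes means, before unblinding. Recover outcomes for patients already censored where consent allows.

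The costs are some tracing work and possibly a less favourable HR and lower power. Recovery will also be incomplete: asymptomatic proximal DVT is a primary component, the scheduled ultrasound is at month 12, and later contact cannot replace a missed scan. The report should state how many patients are affected in each arm.
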